**Hypothesis and specific aims.**

Cystic fibrosis (CF) is a complex, multi-system disease. Increasingly it is becoming clear that colonization of CF airways is due to the presence of a dynamic polymicrobial community that typically includes of a number of pathogenic species [1-3], and that bacterial diversity at this site is strongly influenced by host, environmental and clinical factors. We have shown that CF airway samples have more complex communities than previously appreciated. Moreover, both pediatric and adult CF airway samples possess species associated with colonization of the gastrointestinal (GI) tract e.g. *Enterococcus* spp., suggesting that this host niche may also influence the bacterial community composition of the airways. A growing body of literature and our preliminary data (see below), suggest a strong link between bacterial colonization of the GI tract, immune response and manifestations of chronic airway and GI inflammatory diseases [4, 5]. More recently several studies of both CF and non-CF patients have demonstrated a marked improvement in airway and GI inflammatory outcomes through daily supplementation with specific probiotic bacterial species [6, 7]. We have also demonstrated that the presence of *Lactobacillus casei* in high abundance (through daily supplementation) leads to a restructuring of the infant GI population, which becomes dominated by a number of known beneficial commensal bacterial members (see preliminary data). In addition, we have examined CFTR null mice and shown that their GI microbiota are structured differently and are significantly less diverse compared with wild type animals, a phenomenon we have also demonstrated in CF pediatric patients compared to healthy children (see preliminary data). Finally, previous studies have related changes in GI microbiota associated with obese individuals with increased calorific extraction from ingested food [8], demonstrating that the GI community composition governs its functionality. Given the considerable clinical involvement of the GI and respiratory tracts in CF patients, these recent studies provide a foundation for the overarching hypothesis, that altered GI microbial colonization of CF pediatrics contributes to their health status by influencing: 1. immune response leading to chronic inflammation of the GI and respiratory tracts; 2. airway colonization and 3. weight gain. Further, we hypothesize that manipulation of the GI community composition through daily feeding of a probiotic species, *L. casei*, to CF pediatrics produces a community-wide restructuring of both GI and airway microbiomes associated with improved clinical, immunological and microbiological outcomes.

To examine these hypotheses, a randomized, controlled, double blind multi-center study will be performed to determine the effect of daily supplementation of *Lactobacillus casei sps. Rhamnosus* (*Lactobacillus GG*) on GI and respiratory tract bacterial communities and to relate microbiological changes to primary and secondary clinical and immunological outcomes.

***Specific Aim 1. Define the CF gut microbiome by comparing stool samples from CF pediatric patients at baseline (prior to supplementation) to age matched healthy subjects.***

***Specific Aim 2.*** ***Determine the effect of daily Lactobacillus GG supplementation on GI bacterial communities of CF patients fed probiotic or placebo.***

**Significance.**

It is becoming clear that intestinal microflora is a complex functional unit that lives with the host in a symbiotic relationship. The gastrointestinal tract harbors more than 1000 bacterial species, whose composition is a result of several factors including age, diet, antibiotics and other drugs. The hygiene hypothesis, also known as the theory of “old friends”, implicated intestinal bacteria in the regulation of the immune response [9]. Commensal bacteria drive the immune response by inducing a maturation pattern of dendritic cells that stimulate the regulatory T-cell response. Deficient exposure to the “old friends” or changes in intestinal microecology may lead to an abnormal immune response. There is evidence that a healthy intestinal microflora protects from allergy and other immune disorders [10] by driving the development of immune response toward protection against intestinal and extraintestinal infections, including respiratory infections [11-13].

Children with CF are at risk of an abnormal intestinal microflora, as a consequence of impaired CFTR function, a heavy antibiotic load, pancreatic enzyme supplementation and acid suppression treatment [14]. Our preliminary data (unpublished, see “Preliminary studies section”) indicate that CF patients have a peculiar microbiota. Lung disease, malnutrition and pulmonary inflammation occur very early in life in people affected by CF [15].

The intestine is a site of inflammation in CF. Using immunohistochemistry and intestinal morphometric analysis, Raia et al., identified duodenal mucosal T-cell activation in the absence of alterations of villous architecture in a subset of CF children at-risk of intestinal involvement because of recurrent vomiting or chronic diarrhea who underwent upper endoscopy [16]. The T-cell response was characterized by an increased infiltration of the lamina propria by mononuclear cells expressing ICAM-1, CD25 and IFN-gamma, and by an increased number of villous enterocytes expressing transferrin receptors.

Our hypotheses are supported by preliminary data from our centre. In a subsequent study, the incidence of intestinal inflammation was investigated in a population of 30 CF children, otherwise unselected [6]. Fecal calprotectin and rectal nitric oxide concentration in rectal dialysis bags were used as non invasive markers of intestinal inflammation [6]. It was observed that intestinal inflammation was very frequent in CF. Mean calprotectin values were 4 times above normal in CF children. Nitric oxide rectal production was also increased, which supports the concept that the distal intestine represents a target organ in CF disease. In a trial with the probiotic strain *Lactobacillus rhamnosus* GG (LGG) in children with CF colonized with *Pseudomonas aeruginosa,* calprotectin and nitric oxide concentrations were decreased and values of these inflammatory marker did not return to fully normal values [6].

In a subsequent prospective, randomized, placebo-controlled, cross-over study, we investigated the incidence of pulmonary exacerbations and hospital admissions in CF children colonized with *Pseudomonas aeruginosa* [7]. Pulmonary exacerbations and of hospital admissions were fewer in patients receiving the probiotic LGG than in patients treated with oral rehydration solution (ORS). Probiotics administration also resulted in a slight increase in forced expiratory volume in 1 sec (FEV1). These data suggest that probiotics may delay respiratory impairment in CF children and support a relationship between intestinal and pulmonary inflammation.

Although the evidence available is largely preliminary and should be regarded with caution, our data implicate colonic intestinal microflora in the pathogenesis of CF, as follows:

- Colonic intestinal microflora is changed in CF as a result of changes in intestinal environmental and aggressive therapy.
- Mild to moderate intestinal inflammation is frequent in CF, at least in part, as a consequence of abnormal microflora composition.
- Administration of selected probiotics reduces intestinal inflammation and also exerts beneficial effect on intestinal microbiota .

The intestine, and specifically the intestinal microflora, may therefore be an important target for treatment in CF. The administration of probiotics is a promising treatment approach for children who are on heavy load of antibiotics.

**Experimental Design and Methods.**

***Type of study/setting***

This is a prospective, double-blind, randomized, pilot study comparing oral probiotics versus placebo. The total duration of the study will be 6 months:

- - Patients enrollment: 3 months
  - Treatment phase: 1 months
  - Data analysis and statistical evaluation: 2 months

***Study population***

**Inclusion criteria will be:**

1. A confirmed diagnosis of CF documented by sweat chloride test over 60 mmol/L and confirmed by genotype analysis with the presence of F508del/F508del or F508del/other
2. Boys and girls between 2 and 18 years of age
3. Clinical stability at enrolment, defined as no clinical evidence of acute exacerbation, no modifications in the therapeutic regimen and no hospitalization in the last 2 weeks
4. Pancreatic insufficiency
5. Basal FEV1 above 50% of predicted value

**Exclusion criteria will be:**

1. Colonization of respiratory tract with *Burkholderia cepacia* spp.
2. Steroid therapy within one month before enrolment
3. Pregnancy and fertile women taking oral contraceptives
4. Parenteral or oral antibiotics therapy within 2 weeks before enrolment
5. Regular assumption of probiotics
6. Regular assumption of azythromicin

***Study design***

Study activities are reported in the timeline (Table 1).

| **Parameters** | **Visit 1a** | **Visit 2b** |
| --- | --- | --- |
| Written informed consent | x |  |
| Randomization |  | x |
| Clinical examination | x | x |
| Genetic analysis (if not already performed) | x |  |
| Demographic | x |  |
| Anthropometric | x | x |
| Intestinal inflammation | x | x |
| Microflora |  | x |
|  |  |  |

Study design

Patients meeting the inclusion criteria will be enrolled and randomly assigned to the treatment or placebo group arm. Patients randomized to the treatment arm will receive 6x109 CFU of LGG once a day for a 1-month period. Patients randomized to the placebo group will receive placebo once a day for 1 months. LGG and placebo formulations will be masked and coded appropriately to ensure blindness. LGG formulations will be composed of maltodextrin (163 mg), gelatine capsule (75 mg), LGG (60 mg), magnesium stearate (2 mg). The placebo composition will be maltodextrin (223 mg), gelatine capsule (75 mg) and magnesium stearate (2 mg). LGG and placebo capsules will be identical in appearance, taste and color and only a numeric code will differentiate the two formulations.

For these patients systemic inflammation and intestinal microflora using Fluorescent in situ Hybridization will be evaluated before starting treatment and at the end of it (0 and 1 month

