***Endpoints***

Primary endpoints:

- Modification of intestinal inflammation
- Modification of intestinal microflora composition

***Methods*** .

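### Table 1 marks randomisation and the only microflora sample at Visit 2, but the text beneath it requires samples before and after treatment; followed as tabulated, change in microflora, a primary endpoint, cannot be computed

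*Protocol*

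**What the plan says.** The Study design section of the Protocol presents Table 1 as the timeline of study activities. Its header row is "Parameters | Visit 1a | Visit 2b". Consent, genetic analysis and demographics are marked at the first visit only. Clinical examination and anthropometry are marked at both visits, and so is inflammation: "Intestinal inflammation | x | x". Randomisation is marked at the second visit only: "Randomization | | x". The microflora row has the same pattern, blank at Visit 1 and marked at Visit 2.

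The text below the table gives a different order: "Patients meeting the inclusion criteria will be enrolled and randomly assigned to the treatment or placebo group arm". One month of LGG or placebo follows, and inflammation and FISH microflora "will be evaluated before starting treatment and at the end of it (0 and 1 month" (the bracket is not closed in the text at hand). The section on type of study gives the same duration: "Treatment phase: 1 months".

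Two other places depend on the sampling times. The Endpoints section lists "Modification of intestinal microflora composition" as a primary endpoint. Specific Aim 1 calls for "comparing stool samples from CF pediatric patients at baseline (prior to supplementation) to age matched healthy subjects".

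**The concern.** The table and the text under it disagree on two matters: when children are randomised, and how many microflora samples each child gives. Both matter for the analysis. A modification is a change, so it needs a value before treatment and a value after it. One sample per child gives no change, whichever visit it comes from.

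Site staff usually work from the visit table, and the Protocol itself calls the table the timeline. The aims section describes a multi-centre study, so centres could resolve the conflict differently. A site that takes no microflora sample before the first dose cannot take one later.

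**Working it through.** The point rests on comparing the marks in Table 1 with the text. The only arithmetic is a count of samples.

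**Inputs**
- Table 1: two visits; randomisation at Visit 2 only; microflora at Visit 2 only; inflammation at both.
- Text under Table 1: randomise, treat for 1 month, measure microflora at 0 and 1 month.
- Endpoints: change in microflora and change in intestinal inflammation, both primary.
- Specific Aim 1: CF stool taken before supplementation.
- Visit times: not stated. The letters a and b in the column headers look like footnote marks whose text is not shown.

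**Step 1: samples per child.** Table 1 gives 1 microflora sample and the text gives 2. A within-child change needs 2, so under the table it cannot be computed. This step does not depend on when Visit 2 falls.

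**Step 2: what else follows, for each possible timing of Visit 2.**

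| Item | Visit 2 is the 1-month visit | Visit 2 is the start of treatment |
| --- | --- | --- |
| Randomisation as marked | After treatment has ended, which is impossible | Before treatment, as in the text |
| Microflora sample | After treatment only | Before treatment only |
| Calprotectin samples | One before, one after | None after treatment starts |
| Within-child microflora change | Not computable | Not computable |
| Within-child calprotectin change | Computable | Not computable |
| CF sample for Aim 1 | Missing | Available |
| Between-arm microflora comparison at end of treatment | Still possible | Not possible |

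Neither timing agrees with the text. Under the first, the randomisation mark and the missing baseline sample conflict with it. Under the second, the missing 1-month assessment does.

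**Step 3: the text's intention.** The text under the table names both time points. The section on FISH sample handling also describes microbiota evaluated again after 4 weeks of LGG or placebo, although it is in the past tense and may not describe this trial. The endpoint is worded as a modification. Together these point to paired sampling and to an error in the table.

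**Step 4: sample size.** The one sample size stated, 35 per group, is for intestinal inflammation. It reproduces with a log-odds-ratio formula for two correlated occasions: proportions 0.90 and 0.63, odds ratio 0.189, correlation 0.6, one-sided 0.025, power 0.80.

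n = (1.960 + 0.842)² × [1/(0.90 × 0.10) + 1/(0.63 × 0.37)] / (ln 0.189)² × (1 + 0.6)/2 = 43.6 × 0.8 = 34.9, so 35.

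Nothing in this point changes that figure. If 35 per group were enrolled (an assumption, used only for scale), Table 1 would yield 70 microflora samples and the text 140.

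**Step 5: handling of the baseline stool.** The section on intestinal inflammation has stool frozen at -20°C for calprotectin. The FISH section describes samples fixed in Carnoy's solution and embedded in paraffin. A site following Table 1 at Visit 1 would collect stool for calprotectin but have no microflora mark prompting it to fix a portion for FISH.

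**The case against.** The strongest reply is that this is a clerical slip which no one would act on. The text on the same page is explicit, the endpoint and Aim 1 both imply a baseline sample, and children cannot be randomised after they have been treated. Conversion from PDF may also have lost something: the header letters look like footnote marks, and the lost notes may have given the visit times. The table also ends in an empty row.

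Much of this stands. The visit times cannot be settled from the visible text, and a table error is the likeliest explanation. It does not remove the contradiction. The rows of the table are well formed and the other marks make sense, so nothing visible suggests shifted cells. A footnote giving visit times would settle which column of the comparison applies, but a single microflora mark would remain a single sample.

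A reader might infer three stronger things, and the documents do not support them:
- That Aim 1 is lost in any case. It is lost only if Visit 2 is the 1-month visit. If Visit 2 is the randomisation visit before treatment, its sample precedes supplementation and serves the CF side of Aim 1.
- That the trial has no end-of-treatment assessment. The text provides one at 1 month; it is only the table, under one timing of Visit 2, that omits it.
- That all microflora change data will be lost. That would require every site to follow the table against the text. Even then, if Visit 2 is the 1-month visit, the arms could still be compared at the end of treatment, though that is not the change named as the endpoint.

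**Conclusion.** The contradiction is real and should be corrected before sites work from the table. Table 1 and the text disagree on the timing of randomisation and on the number of microflora samples (1 against 2 per child). Where the table is followed, within-child change in microflora cannot be computed under either timing of Visit 2. This conclusion takes modification to mean change from before treatment.

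The further losses are conditional. With Visit 2 at 1 month, randomisation is out of order and Aim 1 lacks its CF sample. With Visit 2 at the start of treatment, Aim 1 is preserved but neither primary endpoint has a tabulated post-treatment sample. The number of children actually affected cannot be stated, because it depends on how sites resolve the conflict. Sample size and power are unaffected.

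**What to change.** Reconcile Table 1 with the text:
- State the time of each visit in the table.
- Mark randomisation before treatment starts.
- Mark both microflora and calprotectin at month 0, with stool taken before the first dose, and at month 1.
- Say that a portion of the baseline stool is fixed for FISH as the FISH section describes, separately from the portion frozen for calprotectin.
- In the sentence that gives the two time points, reconcile the term systemic inflammation with the endpoint named and assayed elsewhere, intestinal inflammation by fecal calprotectin.

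The cost is small: a corrected table, a few words of text, and one baseline FISH aliquot per child, which the text already calls for. If Visit 2 was meant as the start of treatment, the table also needs a column for the 1-month assessment, which the text again already requires.

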***Endpoints***

Primary endpoints:

- Modification of intestinal inflammation
- Modification of intestinal microflora composition

***Methods*** .

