**Sample Collection and Handling for FISH evaluation**

FISH was performed on fecal samples collected from 22 CF children in stable clinical conditions, 20 age-matched healthy controls. Stools from 10 CF children on antibiotic treatment were also collected and analysed. CF children, in stable conditions, were then treated with LGG (6x109 cfu/die) or placebo for 4 weeks and intestinal microbiota was evaluated again immediately after their administration.. Based on the results obtained by DGGE and RT-PCR, we chose to investigate the presence of *Bacteroides* and *Eubacterium rectale* since both species were consistently reduced in CF children.

*F. prausnitzii* was chosen because it has been associated with the pathogenesis of inflammatory bowel diseases.

Fecal samples, fixed in Carnoy's solution and embedded in paraffin, were cut longitudinally into 4-μm sections, placed on SuperFrost slides (Thermo Scientific, Italy) and incubated with hybridization solution (20 mM Tris–HCl, 0.9 M NaCl, 0.1% SDS and 1% formamide, pH 7.4) with EUB mix positive control oligonucleotide probes (100 ng of EUB I, EUBII and EUBIII). For *Bacteroides*, *E.rectale* and *F. prausnitzii* the slides were incubated with hybridization buffer with 25 ng of their respective FISH probes for 45 min at 50 °C and evaluated by Nikon 80i Eclipse epifluorescence microscope. Using a Nikon DS-U2 color camera and NIS-Elements imaging software (Nikon, Tokyo, Japan). Bacteria were quantified by count within a 10×10–μm area of the microscopic field representative of the region of interest. The oligonucleotide probes used in this study were synthesized by MWG Eurofins (MWG Operon Ebersberg, Germany). All samples were analyzed with the Eub338 mix probe conjugated with fluorescein isothiocyanate (FITC, green signal) at the 5′-end (positive control, which is specific for all bacteria), and an appropriate species-specific probe was conjugated with a single fluorescent carbocyanine (Cy3, red signal) molecule.

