***Specific statistical analysis***

# *Statistical Analysis for primary endpoints*

**INTESTINAL INFLAMMATION:** The binary outcome variable is the presence of at least one intestinal inflammation episode for subject j in cluster i (i=1,..,N, j=1,…n). Based on the results of Bruzzese et al[6], a proportion of subjects with at least 1 episode of intestinal inflammation of 0.90 is expected; a reduction of 30% of such proportion is considered clinically relevant (0.90 vs 0.63). These values determine an odd of experiencing at least one intestinal inflammation episode 0.19 times smaller in the treatment group than in the control group. A intra-cluster correlation coefficient () between the two time occasions of 0.6 is assumed (this is rather a cautionary value because a smaller coefficient is expected) With a one-sided  of 0.025 and a statistical power (1-β) of 0.80, 35 subjects per treatment group are needed to detect such difference in favour of the LGG compared to placebo after twelve months. Alternatively, by using the sample size obtained for powering the analysis of pulmonary exacerbations, all other things being equals, a power of 92% will be reached.

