### *Statistical Analysis of Secondary Endpoints*

***Intestinal inflammation and fecal microflora analysis:*** a descriptive analysis will be performed. Continuous variables will be expressed as mean ± standard deviation (SD), while categorical variables as proportions. The significance of the differences between the groups will be assessed by the chi square test and Fisher’s exact test for dichotomous variables. Continuous variables will be compared with the Student t test and the Mann-Whitney test. A two-sided test was used to indicate statistical significance at a p value of <0.05.

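### Both declared primary endpoints have their only stated tests under the secondary heading, at an unadjusted p<0.05; with four comparisons the family-wise error would be 18.5% under independence

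*Protocol*

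**What the plan says.** All references are to the protocol.

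- **Endpoints** lists two primary endpoints, "Modification of intestinal inflammation" and "Modification of intestinal microflora composition". It gives no order between them and does not say whether one or both must succeed.
- **The section headed "Statistical Analysis for primary endpoints"** deals with intestinal inflammation only. It defines a binary outcome and gives 35 subjects per group at one-sided alpha 0.025 and 80% power. It names no test and does not mention microflora.
- **The section headed "Statistical Analysis of Secondary Endpoints"** opens with "Intestinal inflammation and fecal microflora analysis", so it covers both endpoints declared primary. It calls the analysis descriptive but names chi-square and Fisher tests for dichotomous variables. For continuous ones it says: "Continuous variables will be compared with the Student t test and the Mann-Whitney test". The threshold follows: "A two-sided test was used to indicate statistical significance at a p value of <0.05". No adjustment is mentioned.
- **Sample Collection and Handling for FISH evaluation** names the bacterial targets. It uses "we chose to investigate the presence of" for *Bacteroides* and *Eubacterium rectale*, and adds *F. prausnitzii*, each with its own probe.
- **Intestinal inflammation** (under Methods) gives one measure, fecal calprotectin.

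**The concern.** The same two endpoints are primary in one section and secondary in another. One of them, microflora, has no primary analysis at all. The other has a primary section with a sample size but no test, and a secondary section with tests but a differently stated alpha. Someone following the document cannot tell which comparison decides the trial.

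Two things are at stake. First, a favourable result on any one of several comparisons could be reported as meeting a primary endpoint, each judged at the full 0.05. Second, either endpoint could be called primary or secondary once the data are seen, and the document would support both descriptions.

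**Working it through.** **1. The plan's own figure.** Inputs from the primary-endpoint section: 0.90 vs 0.63, one-sided alpha 0.025, power 0.80, correlation 0.6 between two occasions.

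- Odds ratio: (0.63/0.37)/(0.90/0.10) = 0.189, as stated (0.19).
- Log-odds formula: (1.960 + 0.842)² × [1/(0.90×0.10) + 1/(0.63×0.37)] / (ln 0.189)² = 7.849 × 15.40 / 2.772 = 43.6. Multiplying by (1 + 0.6)/2 = 0.8 gives 34.9, so 35 per group.

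The stated 35 is reproduced. It applies to the binary inflammation outcome only.

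**2. The sections side by side.**

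| Section | Inflammation | Microflora | Alpha | Test named |
|---|---|---|---|---|
| Endpoints | primary | primary | – | – |
| Primary-endpoint analysis | yes | absent | one-sided 0.025 | none |
| Secondary-endpoint analysis | yes | yes | two-sided 0.05 | chi-square, Fisher, t, Mann-Whitney |

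**3. Number of comparisons.** One calprotectin measure plus three FISH targets makes four in total. The three is inferred from the FISH methods; the Endpoints section speaks only of composition.

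**4. Family-wise error if any one success counts and LGG has no effect.**

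- Four independent tests at two-sided 0.05: 1 − 0.95⁴ = 18.5%.
- Upper bound under any dependence: 4 × 0.05 = 20%.
- Equal correlation between the four outcomes (simulated, normal test statistics):

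| Correlation | 0.2 | 0.3 | 0.5 | 0.7 | 0.9 |
|---|---|---|---|---|---|
| Error | 18.0% | 17.4% | 15.6% | 13.1% | 9.4% |

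- Inflammation at one-sided 0.025, three taxa at two-sided 0.05, independent: 1 − 0.975 × 0.95³ = 16.4%.
- Only false positives favouring LGG (0.025 per test), independent: 1 − 0.975⁴ = 9.6%, against 2.5% for a single such test.
- Microflora as one composite test, so two independent tests in all: 1 − 0.95² = 9.75%.

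**5. With control.** Bonferroni across four (0.05/4 = 0.0125 each) gives 1 − 0.9875⁴ = 4.9% under independence and at most 5% otherwise. Holm has the same first step and the same 5% bound.

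**The case against.** The study is called a pilot, and the section with the tests calls its analysis descriptive. Multiplicity rules, a success rule and the choice between the t and Mann-Whitney tests are commonly left to a SAP, which may exist. This stands to a degree: the absence of such detail is not the point here, nor is the lack of a power basis for microflora. A SAP could add an adjustment, but it could not reconcile the labels without overriding one of the protocol's own statements. A descriptive analysis also would not carry a significance threshold.

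The alpha conflict is narrower than it looks. One-sided 0.025 and two-sided 0.05 use the same critical value for a benefit of LGG. They differ in whether a result favouring placebo can be declared significant.

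The 18.5% is near the top of the range. The taxa are counted in stool from the same child, so correlation is plausible, though the protocol gives no value for it. The FISH section is written largely in the past tense, as work already done. It is, however, the only FISH method given, and the Study design section does plan FISH before and after treatment.

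Two stronger readings are tempting and are not supported:

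- A reader might infer four tests for each endpoint, eight in all, which would give 1 − 0.95⁸ = 33.7%. The document names four test procedures overall, two for dichotomous and two for continuous variables. It does not prescribe four per endpoint.
- A reader might infer that the trial's error rate is 19%. That needs independence and an any-one-counts rule, and the protocol states neither.

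**Conclusion.** The contradiction is in the text and holds without any calculation: two endpoints are declared primary, only one is treated as such, and the only tests for both sit under the secondary heading at an unadjusted 0.05.

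The size is conditional. It assumes four comparisons in total, success on any one, and no effect of LGG. The error rate then runs from 9.4% at correlation 0.9 to 18.5% under independence, and cannot exceed 20%. In the direction of LGG benefit it is 9.6% under independence, nearly four times the nominal 2.5%. The label conflict is certain; the count of four is a reasonable inference. The sample size of 35 per group is unaffected.

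**What to change.** Make Endpoints and the two analysis sections agree, in one of two ways.

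**(a) One primary.** Name the binary inflammation outcome that the primary-endpoint section powers as the single primary. State its test and one alpha (two-sided 0.05) in that section, and take inflammation out of the secondary heading. List the three taxa as secondary with Holm (first step 0.05/3 = 0.0167), or as exploratory estimates with 95% confidence intervals.

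**(b) Two primaries.** Specific Aim 2 is about the effect of LGG on gut bacterial communities, so there is a case for keeping microflora primary. Then name the three taxa as the microflora endpoint and apply Holm across the four tests (first step 0.05/4 = 0.0125), or a fixed order with inflammation first.

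**Cost.** Under either option claims on the taxa face a stricter threshold: 0.0167 at the first Holm step under (a), 0.0125 under (b). Under a fixed order they cannot be claimed if inflammation fails. Option (b) with Holm also costs power on inflammation. If that test has to clear two-sided 0.0125, the formula in the working gives (2.498 + 0.842)² = 11.15 in place of 7.849. The requirement becomes 34.9 × 11.15/7.849 = 49.6, so 50 per group. With 35 per group the power is Φ(√(7.849 × 35/34.88) − 2.498) = Φ(0.31), about 62%. The fixed order avoids this loss.

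The change is not only one of wording. A test must be added to the primary-endpoint section, because taking inflammation out of the secondary section would otherwise leave it with none. If continuous calprotectin is made primary instead, the 35 per group must be justified afresh, because it rests on 0.90 vs 0.63.
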